##### Phase II: A Qualitative study

We will conduct a focus-group interview (80 – 90 min.) with 15 - 18 intervention nurses. Investigator nurses (HK or KY) will take the role of facilitator, and use a semi-structured interview guide to explore the role and challenges of the nurses in the patient-centred medication self-management support programme. The questions will include the following issues: i) perceived usefulness of the programme for MBC patients receiving oral chemotherapy, ii) perceived challenges in applying the programme to practice, and iii) perceived patients’ responses to the programme. The focus-group discussion will be recorded and transcribed. Qualitative content analysis will be used, which will include definition of the analytical unit contents, analytical steps taken by a category system, re-checking the category system by applying it to theory and material, and interpretation of the results in relation to the main problem and issue [53].

### Data management

Completed questionnaires will be coded with a participant identification (ID). All research-related documents will be linked by using the participant ID. All study data will be sent to the data centre in PDF format, and will be entered into an Excel file by the data managers at the data centre. The original questionnaires will be stored securely at locked cabinets in outpatient clinics or the nursing department.

### Sample size calculation

The programme will be considered as effective if the proportion of patients who maintain ≥90 % MPR is significantly higher in the intervention group than in the control group, at the completion of 3 months of oral chemotherapy. Previous studies have assumed that adherence has been achieved if the MPR is 70 % in the intervention group and 50 % in the control group [32, 41]. Prospective power analysis revealed that 93 patients were needed in each group for 80 % power at an alpha level of 0.05. Therefore, we plan to recruit 100 patients in each group, for a total of 200 patients.

### Statistical methods

The analysis will be done on the basis of intention-to-treat principle. For the primary outcome, the proportion of patients who maintained ≥90 % MPR in each group at 3 months will be estimated and compared, with adjustments made for allocation factors. If a statistically significant difference is found, our intervention will contribute to medication management in MBC patients. For the other end points, summary statistics will be calculated at each measurement time point in each group and compared between groups. The significance level will be set at 0.05.

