##### Randomisation and blinding

The participants will be randomized to either the medication self-management programme group (intervention group) or the conventional care group (control group) at a 1:1 ratio. The Joint Centre for Researchers, Associates, and Clinicians (JCRAC), an independent, non-profit organisation with extensive experience in conducting clinical trials, will conduct the randomisation by using a computerised random number generator. Randomisation will be stratified according to age (<40 vs. 40≦), treatment regimen (Xeloda vs. Xeloda + Tykerb vs. TS-1), and cancer centre. A database containing patient names will be encrypted and sent to the JCRAC. This is an open-label study; therefore patients, nurses, and investigators will not be blinded.

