##### Patient satisfaction

Patient satisfaction of the medication self-management support programme is measured by two questions developed for this study. 1) Are you satisfied with the medication self-management support programme? and 2) Do you want to continue to receive support from healthcare professionals? The five response options range from ‘not at all satisfied’ to ‘extremely satisfied’. A higher score indicates greater satisfaction.

Baseline measures will be assessed at 1 month after the initiation of oral chemotherapy before randomisation. Health service visit, including emergency department visits and admissions will be collected from medical records, and only treatment change (discontinuation/dose reduction/oral chemotherapy free interval) will be described in a case report form. The study uptake rates and compliance with the intervention will be recorded. Table 2 summarises the measures and timings for each measurement.

**Table 2 Tab2:** Measures and timings for measurements

Measure	Questionnaire	Baseline	2 months	3 months
Demographics	Patient Questionnaire	○		
Medication adherence	MPS	○	○	○
	MMAS-8	○	○	○
Self-efficacy	GSE	○	○	○
QOL	FACT-B	○	○	○
Psychological distress	K6	○	○	○
Symptom severity/interference	MD Anderson Symptoms Inventory	○	○	○

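### Questionnaire scales get only a visit-by-visit group comparison, with no main time point and no stated use of the baseline score or strata, which costs precision and doubles the tests

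*Protocol article*

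**What the plan says.** The Statistical methods section of the protocol article treats two groups of end points differently.

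- **Primary outcome** (proportion of patients with MPR of at least 90% at 3 months): the group proportions "will be estimated and compared, with adjustments made for allocation factors".
- **All other end points**: "For the other end points, summary statistics will be calculated at each measurement time point in each group and compared between groups". No covariates, no model across visits and no main visit are named.
- **Significance**: "The significance level will be set at 0.05". This one level covers everything, and nothing is said about multiple tests.

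The section on patient satisfaction places the baseline assessment before randomisation and refers to the measurement schedule: "Table 2 summarises the measures and timings for each measurement". That table lists MMAS-8, GSE, FACT-B, K6 and the symptom inventory at baseline, 2 months and 3 months. It does not list satisfaction, emergency visits or admissions. Randomisation is stratified by age group, regimen and centre.

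MMAS-8 is described under the primary outcome measure, but the primary analysis is confined to the MPR proportion. MMAS-8 therefore falls under the rule for the other end points.

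**The concern.** The article states a method for the scales, and that method is weaker than the design permits. Each scale has a score taken before allocation, two follow-up scores and known strata. A comparison of group summaries at each visit needs none of the first or the last. Adjustment is mentioned for the primary outcome and, in the same paragraph, not mentioned for the rest.

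Two things are at stake:

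- **Precision.** Variation between patients that the baseline score could explain stays in the error term. Intervals are then wider than they need be.
- **A single answer per scale.** With no main visit, each scale yields a 2-month and a 3-month result of equal standing. The number of tests doubles, and either visit can be emphasised once results are known. This matters more here because the trial is open-label and the scales are self-reported.

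**Working it through.** **1. The plan's own figure.** The inputs from the Sample size calculation section are "the MPR is 70 % in the intervention group and 50 % in the control group" and "93 patients were needed in each group for 80 % power at an alpha level of 0.05". With pooled variance, two-sided 0.05 and no continuity correction:

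n = [1.960·√(2·0.6·0.4) + 0.8416·√(0.7·0.3 + 0.5·0.5)]² / (0.7 − 0.5)² = (1.358 + 0.571)² / 0.04 ≈ 93 per group.

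The stated 93 is reproduced. Power is 80.0% at 93 and 82.8% at 100 per arm. This figure is not in question. The article gives no power statement for the scales.

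**2. Detectable difference on a scale, follow-up score only.** The plan says "we plan to recruit 100 patients in each group, for a total of 200 patients", allocated 1:1. In SD units, for one two-sided test at 0.05 with 80% power:

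(1.960 + 0.8416)·√(2/100) = 2.8016 × 0.14142 = 0.396 SD.

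**3. The same with baseline adjustment.** The ANCOVA variance is (1 − r²) times the follow-up-only variance, so the detectable difference is multiplied by √(1 − r²). The correlation r is an assumption.

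| r (assumed) | Variance ratio | Variance cut | Equivalent sample, 1/(1 − r²) | Detectable difference | Power at an assumed 0.4 SD |
|---|---|---|---|---|---|
| follow-up only | 1 | – | 1 | 0.396 SD | 80.7% |
| 0.3 | 0.91 | 9% | 1.10 times | 0.378 SD | 84.3% |
| 0.5 | 0.75 | 25% | 1.33 times | 0.343 SD | 90.4% |
| 0.7 | 0.51 | 49% | 1.96 times | 0.283 SD | 97.7% |

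A 9% to 51% range for the variance quantity needs care at r = 0.7: the ratio remaining is 0.51 and the cut is 1 − 0.51 = 0.49. The cut over r = 0.3 to 0.7 is therefore 9% to 49%.

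If only 93 per arm were analysed, the follow-up-only figure would be 0.411 SD, and the adjusted range would be 0.392 SD (r = 0.3) to 0.293 SD (r = 0.7). The further gain from adjusting for the strata cannot be sized from the article.

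**4. Number of tests.** Count six scores: MMAS-8, GSE, FACT-B total, K6, symptom severity and symptom interference. The chance of at least one false positive among k independent tests is 1 − 0.95^k.

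- Both follow-up visits: k = 12, 1 − 0.95¹² = 46.0%; expected false positives 12 × 0.05 = 0.6.
- One named visit: k = 6, 1 − 0.95⁶ = 26.5%; expected false positives 6 × 0.05 = 0.3.
- Simulated with assumed correlations of 0.6 between visits of one score and 0.3 between scores: about 38% against 24%.
- Five scores (MMAS-8 set aside, or severity and interference merged): k = 10, 40.1%, against k = 5, 22.6%.

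**The case against.** The strongest reply is that this argues from silence. The article gives these end points one sentence, and comparing groups neither names a test nor rules out covariates. A full protocol or analysis plan may supply them. This stands in part: a reader might infer that the trial will discard the baseline and the strata, but the text does not say so. Non-adjustment is only suggested by the contrast with the primary outcome. What remains is that the sentence does fix a visit-by-visit structure without a main visit, and a plan that followed it faithfully would carry the weakness forward.

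Other stronger readings are also not supported:

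- **That the comparison is biased.** It is not. Randomised groups compared at follow-up give an unbiased estimate, and chance baseline imbalance is already reflected in its interval. The loss is efficiency.
- **That there are 18 tests and a 60% chance of a false positive** (1 − 0.95¹⁸ = 60.3%). This counts the baseline visit. Read literally, the sentence includes baseline, but a difference found before allocation cannot be a false claim of programme effect. The relevant count is 12.
- **That all secondary outcomes are affected.** Satisfaction, emergency visits and admissions have no baseline in Table 2.
- **That the trial's main conclusion is at risk.** Effectiveness is tied solely to the MPR proportion.

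It is also fair that no correlation is given, so the gain may be small, and that the count of six is a reading: MMAS-8 is introduced with the primary outcome, and the symptom inventory text can be read as one averaged score.

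**Conclusion.** The point holds as a worthwhile improvement to the analysis of the questionnaire scales, not as an error of validity. The stated method is unbiased, but it has no single contrast per scale and no stated use of data that the trial already collects.

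The precision cost rests on an assumed r of 0.3 to 0.7, a linear relation between baseline and follow-up, and 100 patients per arm with data. Under these, baseline adjustment removes 9% (r = 0.3) to 49% (r = 0.7, leaving 51%) of the variance, and the detectable difference falls from 0.396 SD to between 0.378 and 0.283 SD. The multiplicity cost rests on six scores: 12 tests against 6, or 46% against 26.5% if independent, and less if correlated. The direction of both does not depend on these choices; the size does.

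**What to change.** For each questionnaire scale:

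- Use ANCOVA or one repeated-measures model, with baseline score, age group, regimen and centre as covariates.
- Make the adjusted difference at 3 months, with its 95% confidence interval, the main contrast. This matches the time point of the primary outcome. Report 2 months as supportive.
- Show baseline values descriptively, without tests.
- Label secondary p-values exploratory.

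If an analysis plan already contains this, it is enough to bring the article's sentence into line with it. Satisfaction, emergency visits and admissions need no baseline term. The cost is a few sentences in the analysis plan and slightly more programming, with no new data, no added visits and no change to the sample size.

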### Research ethics approval

This study was approved by the internal review board of Faculty of Nursing and Medical Care, Keio University (No. 218), and by the three cancer centres. All participants will receive a verbal and written description of the study and be asked to provide informed consent.

## Discussion

The present study will be the first Japanese study to evaluate the effects of a medication self-management support programme on patients with MBC undergoing chemotherapy or targeted therapy. It is characterized by a unique patient-centred approach with the principles of concordance and shared decision-making. A partnership between the patient and the healthcare professional is important in order to facilitate sharing of knowledge and experience with each other to reach an agreement on treatment [54]. Nurses will help patients understand information by using teach-back, set goals with the patients concerning medication management based on patients’ needs and preferences, and help patients solve problems through follow-up counselling.

This mixed-method approach will allow an in-depth understanding of the effects of the medication self-management support programme. In the first phase, the primary outcome in the quantitative study will be assessed by using both objective (MPR) and subjective (MMAS-8) measures. Enhanced patient adherence to medication due to the intervention may lead to positive effects, which will be measured by using a wide range of outcomes including self-efficacy, psychological distress, symptoms, and patient satisfaction. In the second phase, the study will adopt a qualitative evaluation by using content analysis, which will provide practical information from the perspectives of the intervention nurses. A training programme has been developed, and to minimise variability among interventionists, the intervention nurses will be trained on medication self-management of anticancer agents before the study. This programme will also be useful when the intervention is applied in the clinical setting.

It should be noted that performance bias might occur owing to the open-label design of this study. The nature of the study, however, allows for refinement of the intervention in practice. When a patient is aware that adherence is being evaluated, overestimation of adherence in the self-reporting method is a concern. Although the MPR is commonly used to measure adherence, it is only a representation for actual medication use; we do not know whether the medication is actually taken or not. The present study will be carried out at three cancer centres; therefore, further research is needed in other settings to assess generalizability.

As the number of patients undergoing oral chemotherapy continues to increase, there will be a growing need for evidence-based medication self-management support. The present study has the potential to facilitate medication management not only in patients with MBC, but also in those with other types of cancer. The proposed intervention enhances the role of nurses in supporting patients and can be integrated into clinical practice.

## Abbreviations

FACT-B: functional assessment of cancer therapy-breast cancer
GSE: general self-efficacy
JCRAC: Joint Centre for Researchers, Associates and Clinicians
K6: Kessler 6
MMAS-8: Morisky Medication Adherence Scores -8 items
